## Introduction

1

Congenital hearing impairment is the most common congenital disease, with an incidence of about 0.1% to 0.3% in healthy newborns and as high as 2% to 4% in high-risk newborns.^[1]^ The most common risk factors for neonatal hearing loss include central infection, neonatal sepsis, hyperbilirubinemia, perinatal asphyxia and hypoxic encephalopathy, preterm delivery, low birth weight, low Apgar score, prolonged mechanical ventilation, and ototoxic agents. Children with hyperbilirubinemia whose serum total bilirubin level reached the blood exchange indicator are one of the common risk factors for hearing loss in children with Neonatal intensive care unit (NICU).^[2]^ The mechanism of hyperbilirubinemia on auditory impairment is not clear. Some scholars believe that hearing loss is a prominent manifestation of bilirubin neurotoxicity.^[3]^ The brain stem auditory pathway is particularly sensitive to the toxic effect of bilirubin.^[4,5]^ High bilirubin levels can even cause permanent damage to nerve development, mainly including deafness and infant cerebral palsy.^[6,7]^

This study protocol will explore the occurrence characteristics of hearing impairment in neonatal children with hyperbilirubinemia, the relationship between serum bilirubin level, unbound bilirubin and the occurrence of hearing impairment, the mutation characteristics of deafness gene in children with hearing impairment, and the difference between deafness gene and normal population.

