### Participants

2.3

A total of 1000 cases of neonatal hyperbilirubinemia were diagnosed in the full-term neonatal ward of Xiamen Children's Hospital from March 2020 to September 2020.

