#### Inclusion criteria

2.3.1

The inclusion criteria are as follows:

1.Newborn ≤ 28 days, gestational age > 35 weeks, weight ≥ 1.8 kg;2.Apgar score >7 points at 1 minute, 5 minutes, and 10 minutes after birth;3.Neonatal who were first diagnosis as hyperbilirubinemia, not combined with elevated bilirubinemia, will receive the physical audiometry. Hearing screening was completed within 48 hours after admission: distortion product otoacoustic emission (DPOAE) and automatic auditory brainstem response (AABR) were applicable for hearing screening.

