### Data collection

2.4

Neonatal patients (1000 cases) diagnosed with hyperbilirubinemia were selected, and 2 ml of blood was collected from the selected persons. Using second-generation high-throughput sequencing technology, 127 deaf-related genes were sequenced from the collected samples. At the same time, physical audiometry was performed on the selected persons and audiometry data were recorded. Genetic test data and physical audiometry data were correlated and analyzed to find the pathogenic loci of hyperbilirubinemia susceptibility to deafness. For those patients with definite symptoms of hyperbilirubinemia and deafness, and no pathogenic loci were detected in 127 genes, blood was collected from these patients, and total exon sequencing was performed to analyze about 22,000 genes and find new pathogenic loci.

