### Statistical plan

2.5

Excel was used to establish the database, and SPSS 22.0 statistical software was used for statistical analysis in this study.

1.Continuous variable data: for continuous variable data conforming to normal distribution or approximate normal distribution, mean ± standard deviation was adopted to describe the comparison of inter-group differences. When data of continuous variables do not follow normal distribution or variance is uneven, it is expressed as median (quartile spacing) M (P25, P75). Wilcoxon rank sum test in non-parametric test is performed, and multi-independent sample test is performed when there is statistical significance.2.Categorical variables data were described as adoption rate or composition ratio of. Chi-square test was used for comparison of differences between groups, and *P* < .05 was considered statistically significant.3.Logistic regression analysis: physical audiometry results were taken as the dependent variable, and indicators with statistical significance of univariate analysis results were taken as independent variables for binary logistic regression analysis. *P* < .05 was considered as a statistically significant difference.4.ROC curve analysis.

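### Univariate P < .05 is the only way into the logistic model, so bilirubin and remaining confounders can drop out, and null genes can enter if the gene results are screened

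*Protocol article*

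**What the plan says.** Under Statistical plan, the audiometry result is the dependent variable of a binary logistic regression, and "indicators with statistical significance of univariate analysis results were taken as independent variables for binary logistic regression analysis". The threshold for the group comparisons that feed this step is given in the same section: "Chi-square test was used for comparison of differences between groups, and *P* < .05 was considered statistically significant". The regression uses the same level. No covariate is named as always included, and no adjustment for the number of indicators is stated. The fourth item of the section reads only "ROC curve analysis".

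Three other sections bear on this:

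- **Data collection:** "127 deaf-related genes were sequenced from the collected samples", and the genetic and audiometry data are then to be related to each other in order to find susceptibility loci.
- **Introduction and Discussion:** both list the relationship of serum and unbound bilirubin to hearing impairment among the questions to be explored. Both also name preterm delivery, low birth weight and sepsis as risk factors for hearing loss.
- **Inclusion criteria:** these require "gestational age > 35 weeks" and a weight of at least 1.8 kg.

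**The concern.** The same data decide which variables enter the model and then supply its odds ratios. This can go wrong in two directions.

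First, a variable that matters to the question can be lost. A crude P above .05 with few events does not show that bilirubin is unrelated to hearing, or that gestational age, birth weight or sepsis do not confound. The study could then report an adjusted model that omits the exposure it set out to study.

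Second, a long list of genes screened at .05 lets some through by chance, and these would be reported as independent predictors. The abstract's discussion says the findings are meant to guide early deafness-gene screening in infants with hyperbilirubinemia, so chance genes would matter.

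A ROC curve drawn on such a model in the same infants would also look better than it is.

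**Working it through.** The article gives no power, effect size or derivation for its sample size, so there is no figure to reproduce.

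**Inputs from the Protocol article**
- Sample size 1000, all with hyperbilirubinemia (Participants).
- 127 candidate genes (Data collection).
- Threshold .05 (Statistical plan).
- Hearing impairment "as high as 2% to 4% in high-risk newborns" (Introduction). This is a rate for high-risk newborns in general, not for this cohort.

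**Assumed inputs**
- The 2% to 4% rate applies here: 1000 × 0.02 = 20 and 1000 × 0.04 = 40 events. 100 events serves as a sensitivity case, because an early hearing screen may fail more infants than 4%.
- Odds ratio per SD of bilirubin from 1.25 to 2.0.
- Carrier frequency per gene from 1% to 30%.

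**1. Chance that a truly associated bilirubin fails the screen**

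Take bilirubin as normal with equal variance in both groups and SD 1. The mean difference is then ln(OR). With E events, SE = √(1/E + 1/(1000 − E)), and power ≈ Φ(ln(OR)/SE − 1.96), two-sided at .05.

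- E = 20: SE = √(1/20 + 1/980) = 0.226. For OR 1.5, 0.405/0.226 = 1.795 and Φ(−0.165) = 0.435, so the chance of being dropped is 0.565.
- E = 40: SE = √(1/40 + 1/960) = 0.161. For OR 1.5, 0.405/0.161 = 2.51 and Φ(0.55) = 0.71, so the chance of being dropped is 0.29.

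| OR per SD | 20 events | 40 events |
|---|---|---|
| 1.25 | 83% | 72% |
| 1.5 | 57% | 29% |
| 1.75 | 30% | 7% |
| 2.0 | 13% | 1% |

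**2. Null genes passing the screen, if gene results are screened**

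Expected number: 127 × 0.05 = 6.35. Chance of at least one, if independent: 1 − 0.95^127 = 0.9985. With about 6.35 false entries, 20 to 40 events leave 20/6.35 = 3.1 to 40/6.35 = 6.3 events per variable before any real covariate is counted.

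**3. ROC curve, if it scores the selected model in the same data**

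Simulation with 300 runs per setting: 127 independent null carrier indicators in 1000 infants, Pearson chi-square screen at .05, logistic fit on the survivors, then the AUC in the same data and in new data. Ranges run over carrier frequencies of 1%, 3%, 10% and 30%.

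| Events | Mean null genes entering | Apparent AUC | AUC in new data |
|---|---|---|---|
| 20 | 5.1 to 9.5 | 0.58 to 0.83 | 0.50 |
| 40 | 5.6 to 6.9 | 0.54 to 0.74 | 0.50 |
| 100 | 5.1 to 6.2 | 0.55 to 0.67 | 0.50 |

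The number of false entries barely falls as events increase, while the excess in AUC shrinks.

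**The case against.** The strongest case on the other side has five parts.

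- **The ROC item names no marker or model.** A curve for bilirubin alone would fit the aims and would carry no selection optimism. This stands. A reader might infer that the planned ROC is necessarily inflated, but the article does not say it is drawn on the selected model, and validation detail may sit in a fuller plan.
- **The event count is not the plan's figure for this cohort.** This also stands. The Introduction's 0.1% to 0.3% is for healthy newborns, so a reading of 1 to 3 events is not supported here. The 20 to 40 events are an assumption, and more screening failures would lower the chance of losing bilirubin.
- **The article does not say that 127 gene-level indicators enter the regression, and it gives no carrier frequencies.** This stands, so the gene part is conditional and no single AUC value should be relied on. Using Fisher's exact test in sparse cells (the plan names only chi-square) would reduce false entries to roughly 2.5 to 3.3 with 20 events, at carrier frequencies of 0.5% to 10%. The direction is unchanged.
- **Eligibility already controls confounding.** This holds only in part. Low Apgar scores, asphyxia, intracranial infection and ototoxic drugs are handled by the criteria. Above 35 weeks and from 1.8 kg, late-preterm and low-birth-weight infants can still enter, and sepsis is not excluded. The size of the remaining confounding cannot be computed from the document.
- **The study is exploratory, and an article condenses.** Exploratory status lowers the severity. It does not remove the point, because the entry rule is stated, not omitted. A fuller plan could repair it only by overriding it.

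**Conclusion.** The concern holds for the selection rule. Univariate P < .05 is the only stated route into the model, so bilirubin and the confounders left by eligibility can be dropped for lack of crude significance. At an assumed odds ratio of 1.5 per SD the risk for bilirubin is 57% with 20 events and 29% with 40. It ranges from 83% to 1% over the odds ratios and event counts tried.

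Two parts are conditional. About 6.35 null genes are expected to pass only if gene results are among the screened indicators, which the Data collection section suggests but does not state. The AUC is optimistic only if the ROC scores the selected model in the same data. Its true value is then 0.50 when all genes are null, and the size of the excess depends on assumed carrier frequencies and event counts.

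Severity: should be fixed.

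**What to change.** Replace the univariate entry rule with a prespecified model:

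- **Covariates:** always include serum bilirubin. List gestational age, birth weight and sepsis in a stated priority order, and cut the list from the bottom to fit the observed number of events. Fit with Firth penalisation. The list has to be short: at 10 events per parameter, 20 to 40 events support only 2 to 4 parameters.
- **Genes:** add one pooled pathogenic-carrier indicator, or test genes one at a time with multiplicity control. The Bonferroni threshold is 0.05/127 = 0.00039, at which 127 × 0.00039 ≈ 0.05 null genes are expected to pass. A false discovery rate procedure is an alternative. Testing singly at .05 would still expect about 6 false hits.
- **ROC:** state what is scored. If it is a fitted model, report a bootstrap optimism-corrected AUC that repeats every modelling step.

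The cost is revised wording and some analysis outside standard SPSS 22. No new infants or measurements are needed for this change. The downside is fewer significant terms and, if a model is scored, a lower AUC.

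### If every observed carrier of a rare locus is impaired, the planned logistic regression gives no finite odds ratio and a Wald P value near 1; section 2.5 should name a test that survives this

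*Protocol article*

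**What the plan says.** The aim in section 2.4 (Data collection) is to relate genetic test data to audiometry so as to "find the pathogenic loci of hyperbilirubinemia susceptibility to deafness". The sample in section 2.3 is 1000 infants.

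Section 2.5 (Statistical plan) then fixes a two-step analysis:

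- **Screen.** For categorical variables, item 2 says "Chi-square test was used for comparison of differences between groups", at P < .05.
- **Adjusted model.** In item 3, "physical audiometry results were taken as the dependent variable", and the indicators significant in the univariate step "were taken as independent variables for binary logistic regression analysis". The criterion is P "< .05 was considered as a statistically significant difference".
- **Software.** "SPSS 22.0 statistical software was used for statistical analysis in this study".

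Item 3 does not say whether a coefficient is judged by a Wald or a likelihood-ratio test, and it makes no provision for sparse cells. It speaks of indicators without naming loci. However, this regression is the only multivariable method in the plan with audiometry as the outcome, so it is reasonable to read loci as being among the indicators.

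**The concern.** The screen passes forward the loci with the strongest link to impairment. Among rare loci, these include those whose few carriers are all impaired. For such a locus the outcome is quasi-completely separated: no carrier is unimpaired, so the likelihood keeps rising as the locus coefficient grows. Adding covariates does not change this. The log odds ratio has no finite estimate and its standard error becomes enormous. The Wald statistic, estimate divided by standard error, falls towards zero.

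If the coefficient table is then read at P < .05, a locus with overwhelming univariate evidence could appear unrelated to hearing in the adjusted model, with an unusable odds ratio and interval. The Abstract says the results are meant to guide deafness gene screening, so an adjusted result that cannot be interpreted for such a locus matters.

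**Working it through.** The document states no power, effect size or sample-size derivation, so there is no figure of its own to reproduce. The check asks what the planned model returns for plausible tables.

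**Inputs**

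- N = 1000 (section 2.3); threshold .05, taken as two-sided (section 2.5).
- 40 impaired. This is the upper end of the 2% to 4% that the Introduction gives for high-risk newborns. It is a background figure and not a stated rate for this outcome, so 2% to 20% was also tried.
- Carriers per locus and penetrance (the chance that a carrier is impaired) are assumed; the document gives neither.
- Ordinary fit by Newton-Raphson, stopped at 20 iterations (assumed).

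**Step 1: all 5 of 5 carriers impaired.** The table is 5 and 0 in carriers, 35 and 960 in non-carriers.

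- Chi-square = 1000 × (5×960 − 0×35)² / (5 × 995 × 40 × 960) = 120.6, P = 4.7e-28. The locus passes the screen. Fisher's exact test, which does not rely on large cells, gives 8e-8.
- Wald: b = 24.51, SE = 17,975, z = 0.0014, P = .999.
- Likelihood ratio: log-likelihood without the locus = 40 ln(0.04) + 960 ln(0.96) = −167.94. With it = 35 ln(35/995) + 960 ln(960/995) = −151.54. Twice the difference = 32.8, P = 1.0e-8.

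**Step 2: one carrier unaffected, 4 of 5.** b = ln(4×959 / (1×36)) = 4.67. SE = √(1/4 + 1 + 1/36 + 1/959) = 1.13. z = 4.13, P = 3.7e-5. The Wald test works.

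**Step 3: other tables with 40 of 1000 impaired**

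| Carriers impaired | Chi-square P | b (SE) | Wald P | Likelihood-ratio P | Firth P |
|---|---|---|---|---|---|
| 2/2 | 4.1e-12 | 24.43 (28,421) | .999 | 3.2e-4 | 2.4e-4 |
| 3/3 | 1.9e-17 | 24.46 (23,205) | .999 | 9.9e-6 | 9.1e-6 |
| 5/5 | 4.7e-28 | 24.51 (17,975) | .999 | 1.0e-8 | 1.2e-8 |
| 10/10 | 1.2e-54 | 24.67 (12,710) | .998 | 2.7e-16 | 4.7e-16 |
| 2/3 | 2.9e-8 | 3.92 (1.24) | .0015 | .0024 | 9.3e-4 |
| 9/10 | 3.2e-44 | 5.63 (1.07) | 1.4e-7 | 2.4e-13 | 1.7e-13 |

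With 20 to 200 impaired and 1 to 10 carriers, all impaired, the Wald P stays between .998 and 1.

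**Step 4: how often separation occurs.** If carriers are independent, the chance that all k are impaired is penetrance^k. At 90%: 0.9² = 0.81, 0.9³ = 0.73, 0.9⁵ = 0.59, 0.9¹⁰ = 0.35. At 80%: 0.64, 0.51, 0.33 and 0.11.

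**Step 5: with a covariate.** Simulation with N = 1000, 3% background impairment, a bilirubin covariate, 5 carriers and 400 runs per setting:

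| Penetrance | Wald rejects | Likelihood ratio rejects |
|---|---|---|
| 50% | 80% | 81% |
| 80% | 62% | 99% |
| 90% | 43% | 100% |
| 100% | 0% | 100% |

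At 90% the Wald figure matches the chance of avoiding separation, 1 − 0.9⁵ = 41%. A repeat run gave 40%, and there every Wald failure at 90% was in a separated sample.

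**The case against.** The strongest reply is that the plan does not name the Wald test. The same ordinary model judged by likelihood ratio keeps its significance, and the choice between them might sit in an analysis plan that is not shown. That limits the weight of the point but does not remove it. Item 3 fixes the model, entry rule and threshold without qualification, and even under a likelihood-ratio test the ordinary odds ratio and Wald interval remain unusable for a separated locus.

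Three stronger readings are tempting and should be resisted:

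- **That the regression fails whenever nearly all carriers are impaired.** It does not. One observed unaffected carrier restores a finite estimate and a working test. The power loss at 90% penetrance comes from samples in which all carriers happened to be impaired.
- **That the clearest loci would be dropped, leaving the list of loci the wrong way round.** The document nowhere says that a locus is discarded when its adjusted P value exceeds .05. The chi-square result is a declared significance test in its own right and remains strongly positive. A coefficient near 25 with a standard error above 10,000 would also be conspicuous in the output.
- **That separation is to be expected here.** The document gives no carrier counts or penetrance. The Abstract speaks of high-frequency loci and section 2.4 of susceptibility, which could mean more carriers with mixed outcomes. Excluding infants with a family history of deafness may remove some highly penetrant variants. Separation becomes less likely as carriers increase.

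**Conclusion.** The point holds in conditional form. If loci enter the item 3 regression and are judged by the Wald P value, a rare locus whose observed carriers are all impaired yields no finite odds ratio and P near 1 (5 of 5: .999), although it has just passed the chi-square screen and the likelihood-ratio P is about 1e-8. Such a locus could then appear non-significant in the adjusted model; the document does not establish that it would.

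The result for a given separated table is insensitive to the impairment rate. How often such tables arise rests on assumed carrier counts and penetrance: about 73% of samples with 3 carriers and 59% with 5 at 90% penetrance, falling to 35% with 10. This is a modest weakness in the choice of method, worth correcting because the remedy is so cheap.

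**What to change.** Add to section 2.5 item 3, for example:

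> Genetic indicators are judged by the likelihood-ratio test, as the change in −2 log-likelihood when the locus is added as its own block, or by Firth penalised or exact logistic regression, and not by the Wald P value. Where all observed carriers of a locus have the same outcome, the ordinary odds ratio is reported as not estimable, or is replaced by the Firth estimate with its profile-likelihood interval.

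The item should also say explicitly whether loci are among the indicators.

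The cost is wording only, on the same data. The likelihood-ratio block test is available in SPSS 22. Firth or exact regression may need other software, which is the one practical drawback. For 5 of 5 carriers with 40 of 1000 impaired, either route removes the failure: likelihood-ratio P = 1.0e-8, Firth P = 1.2e-8.

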### Ethics and dissemination

2.6

This study has been approved by the ethics committee of Xiamen children's hospital. All participants’ immediate family members will sign the informed consent after being informed about the goals and methods of the study. The present study will be conducted in accordance with the tenets of the 1975 Declaration of Helsinki, as revised in 2000. The result of the study will be disseminated by publication as journal articles.

## Discussion

3

Neonatal hyperbilirubinemia is one of the common diseases in neonatal period, especially in the first week after birth, accounting for about 50% to 75%.^[8]^ Most children have no long-term adverse effects, but hyperbilirubinemia is one of the most important risk factors for hearing loss.^[9]^ To identify and intervene the hearing loss caused by neonatal hyperbilirubinemia timely, effectively, safely, and economically in the early stage, and to reduce unnecessary treatment and waste of medical resources are the efforts of the medical community at home and abroad for many years.

Central infection, neonatal sepsis, hyperbilirubinemia, perinatal asphyxia and hypoxic-ischemic encephalopathy, preterm delivery, low birth weight, and other risk factors for neonatal hearing loss have a much higher incidence of hearing loss than common children.^[10–12]^ What are the mechanisms by which these risk factors contribute to hearing loss? Could it be that something is causing a mutation in the deafness gene that causes deafness? There are few related researches at home and abroad, which is the problem that this study aims to solve. This study protocol will explore the occurrence characteristics of hearing impairment in neonatal children with hyperbilirubinemia, the relationship between serum bilirubin level, unbound bilirubin and the occurrence of hearing impairment, the mutation characteristics of deafness gene in children with hearing impairment, and the difference between deafness gene and normal population.
